#### *Specific Tests and Analysis Plans for Outcomes, by Hypotheses*

***H1: Patients using observed (office-based) MAT induction will have a greater number of days of buprenorphine treatment than patients using unobserved (home) MAT induction at nine-month follow-up.***

The outcomes for these analyses will be the total number of days of buprenorphine treatment during the nine-month follow-up period. The structure of the data is hierarchical (patients nested within practices). Intervention is an indicator variable: 0= home-based induction, 1= office-based induction. Covariates will be included in all models but are not shown here for ease of understanding. Since we anticipate the distribution will be over-dispersed, we will not use a Poisson model. Instead, we will first examine the distribution of the outcome data (counts and/or proportions) and explore alternatives such as negative binomial (or possibly beta binomial on proportions), using model diagnostics and goodness of fit measures to select the best approach. For the negative binomial model, modeling counts ( $Y_{ij}$ ) we have

$$\text{Log}(Y_{ij}) = \gamma_{00} + \gamma_{01}(\text{intervention}) + \gamma_{02}(X_{i.}) + u_{0j}$$

where  $\gamma_{00}$  represents the mean (in terms of logs) for home-based induction;  $\gamma_{01}$  represents the difference between means for the office-based vs home induction group;  $\gamma_{02}$  is the effect of patient level covariates on log counts, and  $U_{0j}$  is a practice random effect. Thus, the intervention effect of office-based vs home induction can be tested as  $H_0: \gamma_{01}=0$  vs  $H_1: \gamma_{01}\neq 0$ .

***H2: Patients using office-based MAT induction will be more likely to take buprenorphine on  $\geq 80\%$  of the days between day 1 and day 270 than patients using home MAT induction.***

The outcome for this analysis will be buprenorphine use on  $\geq 80\%$  of days (yes/no). We will use mixed effects logistic regression models (generalized linear mixed models with logit link) to analyze the data. The model will be similar to that shown above, with a random effect for practice and patient level covariates, along with a fixed effect for intervention group.

***H3: Patients using office-based MAT induction will report greater improvement in quality of life, social determinants of health and social functioning over a nine-month follow-up period than patients using home induction.***

Outcomes for this analysis will be scores on quality of life, social functioning, social determinants of health assessments at baseline, 30 days, 90 days, and 270 days. We will use random coefficient growth curve models to determine whether trajectories on quality of life and other patient reported measures for patients receiving home induction compared to patients receiving office-based induction (time x arm interaction term in mixed model notation).

***H1a, 2a, 3a: Intervention effects on primary outcomes (medication-taking and quality of life) will differ for patients in subpopulations of interest, defined by high executive function, shorter history of substance use, and lower substance use.***

We will conduct exploratory analyses to test for potential effect modification (moderator of intervention effectiveness) by selected patient characteristics. The general hypothesis for these moderator analyses is as follows: The effects of the home versus office-based induction on patient medication-taking (and other primary outcomes) will differ by baseline levels of executive function and substance use (amount and shorter history), dichotomized by baseline scores.

For hypotheses 1 and 2, moderator analyses involve inclusion of main effect for the moderator and a moderator x intervention term. The interaction term tests the differential effect of the intervention on the outcome for subgroups defined by the moderator variable. For hypothesis 3, moderator analyses involve inclusion of the main effects for time, arm, moderator variable, time x arm, time x moderator, arm x moderator, and time x arm x moderator interaction term in the model. The three-way interaction term tests for differential intervention effectiveness by subgroups identified by the moderator variable. Due to the exploratory nature of these analyses, we do not plan to adjust for multiple comparisons in moderator analyses using the subgroups defined above. However, interpretation of results will include reporting on all subgroup analyses and take into account the number of subgroup analyses performed.

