### Hypotheses:

- H1. Patients using observed (office-based) MAT induction will have a greater number of days of buprenorphine treatment than patients using unobserved (home) MAT induction at nine-month follow-up.
- H2. Patients using office-based MAT induction will be more likely to take buprenorphine on  $\geq 80\%$  of the days between day 1 and day 270 than patients using home MAT induction.
- H3. Patients using office-based MAT induction will report greater improvement in quality of life, social determinants of health and social functioning over a nine-month follow-up period than patients using home induction.
- Hypotheses 1a, 2a, 3a: Intervention effects on primary outcomes (medication-taking and quality of life) will differ for patients in subpopulations of interest, defined by high executive function, shorter history of substance use, and lower substance use.

**II. Background and Significance:** Explain the background of this project so that we will understand why it is important to perform this research project. (Approx. 1 page)

The United States faces the worst drug overdose epidemic in its history. Annual deaths from opioid drug overdose now exceed the number of people dying in car accidents. A key driver of the overdose epidemic is a sharp increase in the prevalence of OUD.

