| Moderators 
 
▪ Substance Use History
 
▪ Substance Use Appeal
 
▪ Executive Function
 
 | Patient Surveys completed per clinical care on quality of life*                                                                                                                                                                                                                | 
 
▪ PROMIS short form measures – Appeal and Severity of Substance Use
 
▪ Behavior Rating Inventory of Executive Function–Adult, self-report version)
 
                                                                                                                                                    |

|                                                                                                                                                                                                                                                                                                                                                                                                                                                   |                                                                                                                                                                                                                                                                                                                                             |                                                                                                                                                                                                                          |

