##### *Quantitative Analytic Plan*

After generating initial descriptive statistics on patient and practice characteristics, we will report on differences between: (1) intervention arms and (2) patient dropouts vs. non-dropouts. We will use an intent to treat analysis to assess the effect of the interventions on long-term treatment. We will examine baseline characteristics of patients in both arms using Pearson’s  $\chi^2$  tests for categorical variables and t-tests for continuous variables to assess for unbalanced confounders. Patient engagement in treatment at 30, 90, and 270 days will be analyzed. Given that the comparators employ different strategies that might affect long-term treatment outcomes, we hypothesize that we will observe a difference in outcomes between the two induction strategies. Patient-level covariates will be screened in bivariate analyses and included in multivariate analysis if related to the outcome at  $p<.2$  or are associated with dropout. Covariates (to adjust for potential confounding) and potential moderators will include age, gender, race/ethnicity, comorbidities, and other sociodemographic and health-related variables.

In the event normality assumptions are not met, we will use transformations to normalize distributions, ordinal or Poisson regression where appropriate, and/or the appropriate link function (e.g. logit link for dichotomized measures). We will employ intent to treat analyses using general (generalized) linear mixed models (GLMMs) to incorporate hierarchical and longitudinal data structures. Hypothesis tests will be two-sided with  $\alpha = .05$  or p values reported. Goodness of fit statistics and model fitting diagnostics will be used to assess influential points, outliers, overdispersion and heteroscedasticity and to evaluate alternative model specifications. All statistical analyses will be performed using SAS version 9.4 (SAS Institute Inc., Cary, N.C.).

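### The moderator tests (H1a–H3a) dichotomise graded baseline scores, which loses power in already weak interaction tests if effect modification is roughly linear

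*Protocol*

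**What the plan says.** Section I of the protocol lists H1a, 2a and 3a among its hypotheses. They state that intervention effects differ in subpopulations "defined by high executive function, shorter history of substance use, and lower substance use". Section IV.F (Specific Tests and Analysis Plans for Outcomes, by Hypotheses) then says how the moderators are coded: effects "will differ by baseline levels of executive function and substance use (amount and shorter history), dichotomized by baseline scores".

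The tests are interaction tests. For H1 and H2, "moderator analyses involve inclusion of main effect for the moderator and a moderator x intervention term". For H3 the model adds time: "The three-way interaction term tests for differential intervention effectiveness by subgroups identified by the moderator variable".

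Table 1 (Section IV.D, Surveys) names the candidate tools. Executive function comes from the "Behavior Rating Inventory of Executive Function–Adult, self-report version", and substance use from the "PROMIS short form measures – Appeal and Severity of Substance Use". A footnote leaves the final choice of instruments to discussion with the advisory council. Table 1 also lists substance use history as a moderator, but shows no measure of years of use.

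On status, Section IV.F says: "Due to the exploratory nature of these analyses, we do not plan to adjust for multiple comparisons". It commits to reporting every subgroup analysis and to weighing how many were done. Sample Size and Power covers the arm comparisons only.

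**The concern.** A graded score turned into high and low groups treats patients just either side of the cut as different and all patients within a group as alike. If the arm difference changes gradually along the score, that discards usable information.

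The loss falls on tests with little power to spare. The trial is sized for differences between arms, and an interaction is estimated less precisely than a main effect in the same patients.

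The question also matters to the trial. The Background says that patients and providers ask whether characteristics such as substance use history and executive function favour one induction method. The summary of knowledge to be gained promises an answer. A real gradient that is missed could be read as evidence that the choice of method does not depend on the patient.

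There is a second, conditional issue. If the cut were taken from the enrolled sample, the meaning of high and low would depend on who enrolled.

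**Working it through.** **Inputs from the protocol.** 1:1 randomisation. 500 per arm (N = 1000), or 400 per arm (N = 800) after about 20% attrition. Design differences of 45% vs 54%, and 0.18 to 0.20 SD. "Hypothesis tests will be two-sided with" α = .05.

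**Assumptions, not in the protocol.** Gaussian outcome with residual SD 1, no clustering, one moderator, arm coded ±0.5, and an arm effect that changes linearly with the score.

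**1. The plan's own figures reproduce.**
- 0.18 SD, 500 per arm: SE = √(2/500) = 0.0632; 0.18/0.0632 − 1.96 = 0.886; power 81.2%.
- 0.20 SD, 400 per arm: SE = √(2/400) = 0.0707; 0.20/0.0707 − 1.96 = 0.868; power 80.7%.
- 45% vs 54%, 500 per arm: power 81.3%.

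**2. How weak the planned interaction tests are.** With a 50:50 moderator, the difference between the two subgroup effects has variance 16/N, against 4/N for the main effect, which is four times as large.
- A subgroup difference of 0.18 SD at N = 1000: 0.18/√(16/1000) = 1.423; power 30%.
- A subgroup difference of 0.20 SD at N = 800: 0.20/√(16/800) = 1.414; power 29%.
- Difference detectable with 81% power: 0.36 SD (N = 1000) to 0.40 SD (N = 800), twice the main-effect size.

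**3. Information kept after a split.** Under linear modification, the share kept is the squared correlation between the score and its two-group version. For a normal score cut so that a proportion p lies on one side, this is φ(z_p)² / [p(1 − p)]. At the median it is 0.3989²/0.25 = 2/π = 0.637.

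| Score and cut | Kept | Lost |
|---|---|---|
| Normal, median | 0.637 | 36% |
| Normal, one-third cut | 0.595 | 41% |
| Normal, one-quarter cut | 0.539 | 46% |
| Normal, 20:80 | 0.490 | 51% |
| Uniform, median | 0.75 | 25% |
| Gamma (shape 2), median | 0.554 | 45% |
| Exponential, median | 0.479 | 52% |

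The median is the most favourable cut for a normal score. If the true modification is a step exactly at the cut, nothing is lost.

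**4. What this does to power.** With the score kept continuous, the SE of the interaction slope is 2/√N, or 0.0632 at N = 1000. A slope of 0.177 SD of outcome per SD of score then gives 0.177/0.0632 = 2.80, which is 80% power. A median split multiplies 2.80 by √0.637 = 0.798, giving 2.235. Then 2.235 − 1.96 = 0.275, which is 61% power.

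Simulation with 3000 replicates agrees: 80% against 61% at N = 1000, and 79% against 60% at N = 800.

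**5. The same loss as a sample size.** 1000 × 0.637 = 637 and 800 × 0.637 = 509 effective patients. Recovering the loss by enrolment would need 1/0.637 = 1.57 times the sample.

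**The case against.** Four counter-arguments have weight.

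- **The cut is not stated.** A reader might infer a median or other sample-based split, and so conclude that the subgroups cannot be carried to other practices. The protocol does not say this. Its wording fits an established threshold on either instrument equally well, and a separate statistical analysis plan may name one. The dependence on the sample is therefore only conditional. An external threshold would remove it, but would not remove the information loss.
- **The loss is not one fixed figure.** A reader might take about one third as a property of this plan. It holds only for a normal score, a median split and linear modification. The range in the working is what can be supported.
- **The illustration is not the planned model.** H1 is an over-dispersed count, H2 is a mixed logistic model, and H3a is a three-way term in a growth-curve model. The 80% and 61% figures show the relative cost of splitting. They are not the power of H1a–H3a, for which the protocol states none.
- **Groups have uses.** The choice between home and office is binary, and subgroups are easy to present. The plan also uses proper interaction tests rather than separate tests within subgroups. This supports showing groups but does not require testing with them.

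The length-of-use moderator also needs care. Table 1 shows no graded measure of it, so one cannot assume that a continuous version will exist.

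**Conclusion.** The point holds as a conditional statement about efficiency. Section IV.F does specify dichotomised moderators, the listed candidate instruments give graded scores, and nothing else in the protocol keeps them continuous. This is a stated method that can be improved, not a detail left for later.

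Under approximately linear modification the loss is about 36% for a normal score cut at its median. It runs from about 25% (uniform score) to 50% or more (skewed score or very uneven cut). Under a true threshold at the cut there is no loss, but the protocol does not claim such a threshold.

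A reader might infer that the trial's main conclusions are weakened. They are not. The coding does not enter the arm comparisons, introduces no bias in them, and leaves the stated 81% power intact. The moderator analyses are declared exploratory. Aim 2 concerns characteristics associated with successful treatment rather than effect modification, although H1a–H3a, the Background and the summary of knowledge do raise the latter. Severity is therefore lower: a cheap improvement worth making.

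**What to change.** In Section IV.F, replace the dichotomised moderators with the continuous baseline scores in the terms already specified:

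- Moderator × intervention for H1 and H2.
- Time × arm × moderator for H3, within the planned growth-curve model, whose time structure need not change.
- The same for length of use, if it is collected as a graded measure.

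Check non-linearity, for example with a spline term, and report the estimated arm effect at selected score values. Keep high and low groups for display only, with cuts stated in advance.

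The cost is a change of analysis wording, with no extra patients. No extra data are needed for the scores already planned. The downside is that the main interaction test then assumes an approximately linear change in the arm effect along the score. The non-linearity check addresses this, though such a check itself has limited power.

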#### ***Qualitative Data Analysis:***

Qualitative data from interviews will be recorded, transcribed, and placed into the qualitative software program atlas.ti for analysis. Data will be reviewed for themes and lessons learned. Quotes from the key informant interviews may be used to illustrate a theme but will not be identified. Analysis will be in the form of truth tables. The interview guide will be submitted for COMIRB review when ready, prior to use.

#### **G. Summarize Knowledge to be Gained:**

This study will enable us to assess the impact of two different approaches to MAT induction on long-term treatment engagement and patient-centered outcomes and to determine if certain patient characteristics are associated with more successful treatment engagement based on induction method. With opioid use and drug-related deaths increasing, study findings will be critical and timely. Knowledge gained will guide ongoing efforts to help patients and providers make informed decisions related to MAT expand MAT in primary care settings, improve patient experience, and reduce morbidity and mortality due to opioid dependence and OUD.

